### Data analysis

The average and standard deviation of all relevant variables, including demographic and baseline characteristics, primary and secondary outcomes will be calculated. IIEF-EF and EHS scores will be analyzed using ANOVA with repeated measures throughout the study, in order to compare the trends between the treatment and sham group. GAQ, SEP and success rates will be analyzed and compared between the groups according to Fisher’s exact test in each of the endpoints. The statistical significance will be set at P<0.05.

Demographic characteristics such as age and ED duration will be compared between treatment group and sham group using student’s T-Test. Other demographic characteristics, such as medical background and risk factors will be compared between these groups using Fisher’s Exact Test.

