### Endpoints

The primary endpoint includes changes in the participant’s ability to have penetrative intercourse (without the use of intracavernosal injections, and with or without PDE5i use) from baseline to study completion. This information will be collected using the IIEF-EF questionnaire. The secondary endpoints are sexual activity improvement leading to optimal penetration at follow-ups which will be done according to: (i) Percentage of participants who achieve Minimal Clinically Important Differences (MCID) in IIEF score based on their ED severity at baseline. This is measured using the Change International Index of Erectile Function (IIEF-EF) Questionnaire score; (ii) Change in median International Index of Erectile Function–Erectile Function subdomain (IIEF-EF) from baseline to each follow-up time point in active therapy recipients compared to placebo; (iii) Change in median Sexual Encounter Profile questions number 2 and 3 from baseline to each follow-up time point in active therapy recipients compared to placebo; (iv) Change in median Global Assessment Questionnaire (GAQ) score from baseline to each follow-up time point in active therapy recipients compared to placebo; (v) Change in median Erection Hardness Scale (EHS) score from baseline to each follow-up time point in active therapy recipients compared to placebo; (vi) Changes in duplex ultrasound parameters from baseline to study completion in active therapy recipients compared to placebo.

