## Figures and Tables

**Figure 1: F1:**
[figure not shown]
A) Shockwave therapy being administered; B) Shockwave therapy machine for treatment group; C) Shockwave therapy machine for control/ placebo group.

**Table 1: T1:** The details of the events and procedures participants will undergo throughout the trial.

Schedule of events	Screening	Weekly treatment					Monthly treatment				Follow-up
Visit	Visit 1	Visit 2	Visit 3	Visit 4	Visit 5	Visit 6	Visit 7	Visit 8	Visit 9	Visit 10	Visit 11
Time point	Screening	Week 1	Week 2	Week 3	Week 4	Week 8	Week 12	Week 16	Week 20	Week 24	Month 12
Activity window	0–30 days pre	± 3 days	± 3 days	± 3 days	± 3 days	± 3 days	± 7 days	± 7 days	± 7 days	± 7 days	± 30 days
Informed consent	•										
Medical and urological history	•										
Demographics	•										
Physical examination	•										
Penile Doppler ultrasound	•										•
Blood Test: CBC, HbA1c, PSA and Testosterone	•										
Questionnaires: IIEF-EF, GAQ, SEP, EHS	•	•	•	•	•	•	•	•	•	•	•
Verification of eligibility	•										
Randomization		Group A: Treatment Group B: Sham									
Administration of therapy		•	•	•	•	•	•	•	•	•	
Review concomitant medication		•	•	•	•	•	•	•	•	•	
Review adverse events		•	•	•	•	•	•	•	•	•	•

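### Four of the six secondary endpoints are defined as changes in medians, but the planned analyses compare means or proportions

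*Protocol article*

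**What the plan says.** The Endpoints section of the protocol article lists six secondary endpoints. Four are expressed through a median, each compared between active and placebo recipients:

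- (ii) "Change in median International Index of Erectile Function–Erectile Function subdomain (IIEF-EF) from baseline to each follow-up time point"
- (iii) "Change in median Sexual Encounter Profile questions number 2 and 3 from baseline to each follow-up time point"
- (iv) "Change in median Global Assessment Questionnaire (GAQ) score from baseline to each follow-up time point"
- (v) "Change in median Erection Hardness Scale (EHS) score from baseline to each follow-up time point"

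The other two are not. Endpoint (i) is "Percentage of participants who achieve Minimal Clinically Important Differences (MCID) in IIEF score based on their ED severity at baseline", and endpoint (vi) is "Changes in duplex ultrasound parameters from baseline to study completion in active therapy recipients compared to placebo".

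The Data analysis section plans means and standard deviations for all outcomes. It then says "IIEF-EF and EHS scores will be analyzed using ANOVA with repeated measures throughout the study", with the aim of comparing trends between the arms. GAQ, SEP and success rates go to Fisher's exact test. No median summary and no median-based test is mentioned, and the Abstract repeats the pairing of ANOVA with Fisher's test.

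Table 1 marks the row "Questionnaires: IIEF-EF, GAQ, SEP, EHS" at all 11 visits: screening, nine treatment visits and Month 12.

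**The concern.** The article names one quantity when it defines these endpoints and another when it analyses them. A reader of the results could not tell whether an IIEF-EF or EHS effect is a difference in medians, as defined, or in means, as tested. For SEP and GAQ the category that Fisher's test would count is also open. The choice affects the size of the reported effect, and leaving it open allows it to be made after the data are seen.

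The time structure does not match either. The definitions ask for a comparison at each time point, whereas the stated purpose of the ANOVA is to compare trends. A test of overall trend does not by itself give the between-arm difference at Month 12.

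A second matter depends on how the ANOVA is run. In its classical form it needs every visit from every man, and the Participants section expects drop-out for reasons that may be related to outcome.

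**Working it through.** **The plan's own figure.** The sample size of 189 rests on the primary binary endpoint (20% against 40%, power 80%, significance 5%, 63 control and 126 active). Take a two-sided test, pooled variance, no continuity correction and k = 2 active men per control. The pooled rate is (0.20 + 2 × 0.40)/3 = 1/3, and

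n(control) = [1.96 × √(1.5 × 1/3 × 2/3) + 0.8416 × √(0.16 + 0.24/2)]² / 0.20² = (1.1316 + 0.4453)² / 0.04 ≈ 62.2.

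This rounds up to 63, giving 63 + 126 = 189. The figure is reproduced, and nothing below changes it.

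**Definition against analysis.**

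| Secondary endpoint | Quantity defined | Analysis named | Agree? |
|---|---|---|---|
| (i) MCID in IIEF | percentage | Fisher's test, if counted among success rates | yes |
| (ii) IIEF-EF | change in median | repeated-measures ANOVA (means) | no |
| (iii) SEP 2 and 3 | change in median | Fisher's test, category not stated | no |
| (iv) GAQ | change in median | Fisher's test, category not stated | no |
| (v) EHS | change in median | repeated-measures ANOVA (means) | no |
| (vi) Ultrasound | change, no median named | no test named | not affected |

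The mismatch covers four of the six.

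**Does mean or median matter?** Two illustrations use the article's 20% and 40% as responder shares.

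1. *Score with responders (assumed distribution).* Responders gain 12 points on average (SD 3) and the rest gain 1 (SD 2). The means are 0.2 × 12 + 0.8 × 1 = 3.2 and 0.4 × 12 + 0.6 × 1 = 5.4, a difference of 2.2. Simulated medians (400,000 draws per arm) are 1.63 and 2.93, a difference of 1.30. The median contrast is about 1.30/2.2 = 59% of the mean contrast.
2. *Two-category item (assumed format).* Both shares are below 50%, so the median falls in the non-response category in both arms. The difference in medians is zero, while the proportions differ by 20 percentage points.

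**Complete cases, if the ANOVA is run that way.** The documents give no missed-visit rate. Let m be an assumed rate, independent across the 11 visits. The expected number of complete cases is 189 × (1 − m)^11.

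| m (assumed) | (1 − m)^11 | Men kept of 189 |
|---|---|---|
| 1% | 0.895 | 169 |
| 2% | 0.801 | 151 |
| 3% | 0.715 | 135 |
| 5% | 0.569 | 108 |

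Independence is the unfavourable case. If the same 5% of men accounted for every missed questionnaire, 5% would still be missing at each visit, but 0.95 × 189 ≈ 180 men would be complete.

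**The case against.** The strongest reply is that a journal article condenses the protocol. Missing-data handling, sphericity correction, covariance structure and visit contrasts are normally settled in an analysis plan, which is not shown here. For those items the reply stands: their absence is no finding, and a group-by-time ANOVA can be followed by contrasts at single visits. It does not answer the median question. The article states both the endpoint and the analysis, and they conflict, so an analysis plan could follow one section only by departing from the other.

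Three stronger readings are tempting and are not supported:

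- A reader might infer that the ANOVA will drop every man with a missed visit and that a large share of the sample will be lost. The article names no algorithm and no complete-case rule, and the loss depends on an assumed rate and on independent misses. Drop-out of the kind listed in the Participants section would concentrate misses in the same men and so leave more complete cases.
- A reader might infer that all secondary endpoints are affected. Endpoint (i) is a percentage that Fisher's test suits, and (vi) names no median.
- A reader might infer that SEP and GAQ are yes/no items, so that their medians are uninformative. The article gives no response format, calls GAQ a score and schedules it at screening. The two-category example above is therefore only an illustration.

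**Conclusion.** The contradiction between the Endpoints and Data analysis sections is plain on the text and holds for IIEF-EF, SEP 2 and 3, GAQ and EHS. As written, the tests would not estimate the stated quantities.

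The documents do not fix the size of the consequence. The gap of 2.2 against 1.3 points comes from an assumed mixture and shows only that the two quantities can differ materially. The loss of men is a conditional risk: it arises only under a complete-case ANOVA, and the range from 169 to 108 kept rests on assumed independent misses of 1% to 5% per visit.

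The point concerns secondary endpoints only. It should be corrected, but it does not threaten the primary comparison.

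**What to change.** State one quantity per endpoint in both sections, with a matching analysis.

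- **IIEF-EF and EHS:** define as mean change from baseline. Analyse by a mixed model for repeated measures on all randomised men with available data, with treatment, visit, treatment-by-visit and baseline score. Name the Month 12 between-arm difference with its 95% confidence interval as the contrast of interest. With screening as baseline there are ten later visits, so an unstructured covariance has 10 × 11/2 = 55 parameters and the sham arm has 63 men. Pre-state a simpler structure in case the model does not converge.
- **SEP 2 and 3, GAQ:** define as the proportion in a pre-stated response category at each post-baseline visit. Keep Fisher's test or use a logistic model adjusted for baseline.

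The mixed model uses every available visit, so a single missed questionnaire no longer excludes a man under any reading of the plan.

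The cost is revised endpoint wording and a little more analysis work on the same data. The article lists the trial as awaiting IRB approval, so on its own stated status the change is cheap. The primary endpoint and the 189 stay as they are.

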## INTRODUCTION

The surgical procedure of radical prostatectomy is associated with damage to the Cavernous Nerves (CN) and erectile dysfunction. Each year there are approximately 250,000 newly diagnosed cases of Prostate Cancer (PCa) in the United States; overall, it is estimated that 15.3% of all men will be diagnosed with PCa at some point during their lifetime. Radical Prostatectomy (RP) is a common surgical treatment used for localized PCa. Although the long-term oncologic outcome following RP are good, a significant number of patients suffer from post-surgical lower urinary tract complications, including incontinence and ED [1–4]. In most patients, incontinence resolves within 3-months. However, ED may persist for years, and many patients never fully recover erectile function. The prevalence of ED following RALP is a significant concern, with studies indicating a substantial impact on men’s sexual health. Current research suggests that approximately 80% of men may experience varying degrees of ED after undergoing RALP [2], highlighting the high number of men affected by this condition in the post-surgical period. Despite advancements in surgical techniques and the implementation of nerve-sparing approaches, ED remains a prevalent and challenging consequence for a substantial majority of individuals who undergo RALP.

Nerve injury is recognized as a key-factor in the development of post-surgical erectile dysfunction. Even though nerve-sparing techniques are now routinely practiced when performing RP, CN injury, as a result of thermal damage, ischemic injury, mechanically induced nerve stretching and inflammatory effects, remains a major factor in development of ED following surgery. Compounding the acute effects of RP on erectile function, the loss of stimulatory neuronal signals that initiate spontaneous erections results in an overall reduction in oxygenation of erectile tissue, which leads to progressive changes in penile architecture that include induction of smooth muscle apoptosis, fibrosis and deposition of collagen. The effects of long-term ED on penile architecture are such that even when there is CN regeneration, erectile function cannot be fully recovered. Prevention of chronic ED following RP is often considered a race in time between CN regeneration versus irreversible changes in penile architecture.

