### Participants

The inclusion criteria are as follows: (i) Be willing and able to provide informed consent; (ii) Be male; (iii) Be ≥ 40 and ≤ 75 years of age (inclusive); (iv) Undergo radical prostatectomy for prostate cancer (nerve sparing or non-nerve sparing without neoadjuvant chemotherapy or radiation therapy.); (v) Be at least six weeks post radical prostatectomy; (vi) Be in a stable sexual relationship for over 3 months prior to enrollment; (vii) Have a serum testosterone level of 300 ng/dL-1000 ng/dL within 1 month prior to enrollment; (viii) Have a HbA1c level ≤ 7% within 3 months prior to enrollment; and (ix) Have undetectable PSA value at the time of enrollment. Patients of all prostate cancer grades/stages and Gleason scores will be included as long as no adjuvant or salvage treatment is needed. Patient drop out will be due to patient preference, adverse effects, cancer recurrence, or need for further cancer treatment.

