### Sample size calculation

In our research protocol, we aim to assess the effectiveness of shockwave therapy on patients’ ability to engage in penetrative intercourse after a one-year period. Our initial observations revealed that 20% of patients achieved this without therapy, whereas an aim of 40% will achieve it with shockwave therapy. To design our study with statistical rigor, we utilized an allocation ratio of 2:1 (control:shockwave), and factored in a power of 80% and a significance level of 5%. Employing calculated Z-values for α and β, we derived an estimated sample size requirement of approximately 189 participants. The overall sample size was determined to be 189 patients, with 63 patients in the control group and 126 in the active treatment group.

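### The primary success rate is tested by an unadjusted Fisher's exact test, which is valid but gives up power that adjustment for nerve-sparing status, baseline IIEF-EF and age could recover

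*Protocol article*

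**What the plan says.** **Primary test.** The protocol article, Data analysis, says "GAQ, SEP and success rates will be analyzed and compared between the groups" according to Fisher's exact test. The Results paragraph of the abstract likewise assigns Fisher's test to categorical variables and covers the primary as well as the secondary outcomes. Neither place names a covariate or a stratum.

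**Population.** The Participants section admits men after prostatectomy that was "nerve sparing or non-nerve sparing without neoadjuvant chemotherapy or radiation therapy". The Introduction states: "Nerve injury is recognized as a key-factor in the development of post-surgical erectile dysfunction". It adds that PDE5 inhibitors work through functional cavernous nerves, and the Endpoints section lets the primary endpoint be met with or without a PDE5 inhibitor.

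**Baseline data.** Table 1 marks demographics, medical and urological history, and the IIEF-EF questionnaire at screening. The only stated use of baseline differences is a set of significance tests: "Demographic characteristics such as age and ED duration will be compared between treatment group and sham group" by t-test, and medical background and risk factors by Fisher's test.

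**Sizing.** The Sample size calculation assumes that "20% of patients achieved this without therapy, whereas an aim of 40% will achieve it with shockwave therapy", with 80% power and a 5% significance level, and arrives at "63 patients in the control group and 126 in the active treatment group".

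**The concern.** The plan's own rationale implies that cavernous nerve damage strongly influences whether a man regains penetrative intercourse. Two surgical populations that differ on this factor are nevertheless pooled in a test that ignores it. If the factor is prognostic, leaving it out costs power. Any chance difference in the nerve-sparing mix between 63 and 126 men also passes straight into the observed success rates. Comparing baseline characteristics by p-value does not help, because it leaves the estimate of the treatment effect unchanged.

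What is at stake is efficiency. The total of 189 contains no allowance for dropout, although the Participants section lists reasons for it, so power that can be gained without more patients is worth having.

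**Working it through.** **Inputs from the protocol article.** Success 20% sham and 40% active; 80% power; 5% significance (sidedness not stated; two-sided reproduces the total); 63 sham and 126 active.

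**Inputs not in the documents, therefore assumed.** The share of nerve-sparing surgery, its effect on success, and the prognostic strength of baseline IIEF-EF.

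**1. The plan's own figure.** Pooled-variance formula for two proportions, no continuity correction, active arm twice the sham arm:

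n(sham) = [1.960 × √(p̄(1−p̄)(1+1/2)) + 0.842 × √(p₁(1−p₁) + p₂(1−p₂)/2)]² / (p₂−p₁)²

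- p̄ = (0.20 + 2 × 0.40)/3 = 0.333, so the first root is √(0.2222 × 1.5) = 0.577
- the second root is √(0.16 + 0.12) = 0.529
- n = (1.960 × 0.577 + 0.842 × 0.529)² / 0.04 = 1.577² / 0.04 ≈ 62.2, rounded up to 63

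63 + 126 = 189, as stated.

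**2. Power of the test that the plan names.** Summing the two binomial distributions over every table with p < 0.05, at 63/126 and 20% versus 40%:

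| Test | Power |
|---|---|
| Fisher's exact (planned) | 78.8% |
| Chi-square, unadjusted, uncorrected | 81.1% |
| Normal-approximation formula used for sizing | 80.6% |

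Fisher's actual type I error is 3.9% at a common success rate of 20% and 4.1% at 30%. This conservatism is why it has less power than chi-square.

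**3. Stratifying by nerve-sparing status (simulation, marginal rates held at 20% and 40%).**

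| Assumed share and success (nerve-sparing / non-nerve-sparing) | Implied odds ratio for nerve sparing | Mantel-Haenszel, uncorrected |
|---|---|---|
| 75%; moderate effect | about 2.6 | about 82% |
| 75%; sham 25%/5%, active 50%/10% | 6.3 sham, 9 active | about 84% |
| 60%; sham 30%/5%, active 60%/10% | 8.1 sham, 13.5 active | about 88% |

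The odds ratios follow from the rates. For example, (0.25/0.75)/(0.05/0.95) = 6.3 and (0.60/0.40)/(0.10/0.90) = 13.5. Compared with chi-square at 81%, stratification itself adds about 1, 3 and 7 points. The remaining 2 points or so of each gain over Fisher come from leaving Fisher. With a continuity correction, Mantel-Haenszel falls to 77.5%, 79.5% and 83.0%, so the version of the test matters.

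**4. Adjusted logistic model (likelihood-ratio test; arm, nerve-sparing status and baseline score; nerve-sparing share 70% or 85%).**

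| Assumed prognostic strength | Power |
|---|---|
| Neither covariate prognostic | 81–82% |
| Nerve sparing only, odds ratio 2 to 5 | 83–84% |
| Nerve sparing odds ratio 3, baseline log-odds 0.5 per SD | about 85% |
| Nerve sparing odds ratio 3 to 5, baseline log-odds 1.0 per SD | 88–90% |

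Simulated type I error was 4.3% to 5.9%, averaging about 5% (Monte Carlo standard error 0.4 points). No scenario lost power against Fisher.

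**5. Chance imbalance without stratified allocation.** At an assumed 70% nerve-sparing share, the SD of the between-arm difference is √(0.7 × 0.3 × (1/63 + 1/126)) = √0.005 = 7.1 points. The chance of a difference of 10 points or more is about 19%, 14% and 3% at shares of 60%, 75% and 90%.

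**The case against.** The strongest reply is that nothing here is an error. Fisher's test is valid under randomisation, its type I error already allows for chance imbalance, and it matches a sample size built on an unadjusted comparison. Power of 78.8% is so close to 80% that the trial is not mis-sized. All of this stands.

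Several stronger readings are tempting, and the documents do not support them:

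- **That randomisation is unstratified.** The article says only that computer software allocates 2:1. Stratification factors are detail that an article commonly leaves to the full protocol, so its silence shows nothing.
- **That the gain is 5 to 9 points.** This needs odds ratios of roughly 6 to 13.5 for nerve sparing and counts the 2 points from abandoning Fisher. With a moderate effect, stratification adds about 1 point over chi-square.
- **That baseline IIEF-EF will bring a large gain.** It is measured about six weeks after surgery. If scores then cluster near the floor, which the documents do not settle, it adds little.
- **That adjustment removes chance imbalance at no cost.** It corrects only for the covariates in the model. The exact error guarantee is lost, and a logistic odds ratio is not the 20% versus 40% contrast unless it is standardised.

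A further reply is that covariate adjustment belongs in a statistical analysis plan that is not shown. That would excuse silence, but this document is not silent. It names the test for the success rates, and an adjusted primary analysis elsewhere would conflict with it.

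**Conclusion.** The point holds as a matter of efficiency. The article fixes an unadjusted test although its own rationale points to a prognostic factor and candidate covariates are collected at screening. Moving from Fisher's test to a pre-specified adjusted analysis raises power from 78.8% to at least about 81%. It reaches about 82–84% if nerve-sparing status is moderately prognostic, and 84–88% if it is strongly so and the Mantel-Haenszel test is used. Up to about 90% is possible if baseline IIEF-EF is strongly prognostic as well.

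Only the 78.8% and 81.1% follow from the documents' figures. Everything above them rests on an assumed nerve-sparing share and assumed prognostic strength. A reader should not infer that the planned test is invalid or that 189 patients is miscalculated.

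**What to change.** - Pre-specify as the primary analysis a logistic regression of Month 12 success on arm, nerve-sparing status, baseline IIEF-EF and age.
- Report the standardised risk difference with its 95% CI, which keeps the result on the 20% versus 40% scale of the sample size calculation.
- Keep Fisher's exact test as a sensitivity analysis.
- Record nerve-sparing status explicitly under urological history. Table 1 does not list it as an item, although the eligibility criteria refer to it.
- State in advance the form of each covariate and how missing baseline values are handled.
- Show baseline characteristics descriptively. The significance tests between arms add nothing to the primary estimate.

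**Cost.** A change of analysis wording and one explicit data item, with no extra patients or visits. Fisher's exact type I guarantee is replaced by an approximate one, simulated at about 5%. The article gives the trial status as pending IRB approval, so the model can still be fixed before any outcome is seen.
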